### Phase 1: designing the intervention

The intervention will be informed by the extant literature regarding the pragmatics and focus for the couple work. It will consist of six sessions [34,35] conducted every two to three weeks [28,47] by registered practitioners at a local voluntary sector counselling organisation. The intervention will be delivered off-site in central Edinburgh, away from the pressures of a busy outpatient hospital clinic where there is usually limited time to discuss psychosexual concerns during healthcare consultations [24].

The content of the intervention will comprise assistance with emotional disclosure [33,48], psycho-education [19,29], relational and sexual needs [29-31] and dyadic adjustment and coping [49,50]. A treatment manual will be developed to guide delivery of the intervention [51]. The manual will comprise information about prostate cancer and its effects, principles of therapeutic change, guidance on using the manual and a detailed session structure plan. This manual-based family-relational-psychosexual support will be based on systemic principles [52-55] combined with techniques from sex therapy, that is, sensate focus [56]. Therefore, the manual aims to integrate components of systemic theory with elements of sex therapy to support intimacy and emotional aspects of the couple relationship.

Specialist training in delivery of the intervention will be provided to practitioners holding accredited counselling or psychotherapy qualifications. Training will include sessions led by men affected by prostate cancer and a systemic practitioner in cancer care. Fidelity to the manual will be assessed as an ongoing process, recorded by practitioner self-report using a checklist provided by the research team.

In line with routine counselling interventions, this study adopts a waiting-list control design [57]. The control group will be offered the intervention if the analysis indicates a significant benefit in quality of life for couples who receive the support.

The session structure for the intervention will cover six main topic areas as follows:

**Session 1 - Getting to know the couple: orientation and engagement.** This first session will outline the support on offer. Topics for discussion will include:

● the couple’s definition of current issues, concerns and problems

● the cancer diagnosis and treatment(s)

● the partner’s role in the context of diagnosis and treatment

● mapping the support network and wider family system

**Session 2 - The couple’s communication style and relationship.** This session is primarily focused on understanding the patient and their partner as a couple, to explore how they convey love, support, understanding, companionship and affection.

**Session 3- Intergenerational patterns of illness, coping and affection.** Focusing on intergenerational patterns, discussion will centre on the role and meaning of illness in the couple relationship in the context of:

● family resilience

● dyadic adjustment in ill-health

● the role of partners and family when someone is ill

● how people in the family express intimacy

**Session 4 - Couple intimacy before and after cancer.** Intimacy before and after cancer will be explored. A psycho-educational approach will be used to promote closeness and express intimacy after treatment. The place of medical treatments will be considered and techniques from sex therapy will be applied if appropriate for the couple.

**Session 5 - Further exploration of emerging areas.** This session will focus on areas that have emerged in previous sessions where the practitioner and couple wish to give more time to them. This may include more work on increasing levels of intimacy, and improving satisfaction with sexual activity, with discussion of successes or challenges therein.

**Session 6 - Summarising the couple’s accomplishments and future planning.** The final session will summarise work to date, with discussion of relapse prevention and how to take forward progress that has been made, including the setting of short- and long-term goals. This will include a specific focus on maintaining intimacy and dyadic adjustment.

### Phase 2: determining the parameters for a definitive trial

#### Patient recruitment

Eligible patients will be identified from the urology surgical lists at the Western General Hospital, Edinburgh, UK. The research nurse at the site will apply eligibility criteria before patients are invited to complete the EPIC questionnaire. Patients will be invited to complete the questionnaire via two routes: either on-site at their post-operative follow-up appointment at the outpatient surgical urology follow-up clinic; or by postal invitation from the clinical team.

The recruiting site will complete logs to report recruitment rates at baseline and any attrition following randomisation. Additionally, attendance at the couple support sessions will be logged to assess attrition rates at each stage of the intervention. The recruitment rate for a larger definitive trial will be calculated from the time taken for 68 couples to complete the study.

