### Setting and participants

Patients with prostate cancer and their partners are being recruited from a single site in one National Health Service (NHS) board: an outpatient surgical urology clinic at the Western General Hospital, Edinburgh (NHS Lothian), UK. The recruiting clinic sees patients from a wide catchment area covering four Health Boards in Scotland: the Borders; Dumfries and Galloway; Fife; the Lothians. Recruitment will take place over one year.

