#### Sample size calculation

The trial aims to recruit 68 men and partners at routine follow-up after surgery, with 30% over-recruitment to enable adjustment for loss to follow-up [43]. A sample size of 68 couples was calculated using G-Power [44] based on having 90% power to detect a small-to-medium effect size *f* of 0.20 on the primary outcome (using repeated measures analysis of variance (ANOVA) and testing the within-between group interaction in this two-group design with two points of measurement (end of intervention and six-month follow-up) at an alpha level of 0.05). A small-to-medium effect on sexual function was selected based on previous intervention effects seen for couple interventions in the cancer literature [45].

Assuming a baseline mean of 33 and a standard deviation of 24 on the sexual function subscale of the EPIC [46], this study will have 90% power to detect a mean difference of 9.6 units at the 0.05 level. This will allow the study to estimate the efficacy of this intervention on the mean difference in overall sexual function (as measured by EPIC) between the intervention and control groups pre- and post-test. The standardised difference observed will be used to calculate the sample size required for a definitive trial to test the efficacy of this intervention. The anticipated effect size of *f* of 0.20 on the primary outcome is a crude estimate, as it is based on a pooled estimate of a heterogeneous selection of couple interventions for several types of cancer [45].

Based on surgical data from the locale (2009 to 2011) we estimate that there will be 500 patients who will be between 12 weeks and two years from surgery during the one-year recruitment period. The estimated recruitment rate from a prior study with a similar population and intervention design was 21% [33]. As some of the patient population will be excluded from the study based on the eligibility criteria above, we anticipate contacting approximately 420 patients to recruit 88 couples (taking account of 30% over-recruitment [43] to achieve a sample size of 68 couples completing the study).

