#### Outcome measures

The primary outcome measure (see below) assesses sexual functioning as part of a broader health-related quality-of-life measure. The secondary measures reflect the evidence that men and their partners require psychological (anxiety, depression), relational and sexual components to an intervention to meet the needs of this group.

Primary outcome measure

● Sexual functioning - EPIC measures general and sex-specific items related to prostate cancer [46]. EPIC is a comprehensive instrument that evaluates patient function and ‘bother’ after prostate cancer treatment. Potency of ≤60 in the sexual function domain is a clinical cut-off [42].

Secondary outcome measures

● Anxiety and depression - Hospital Anxiety and Depression score (HADS) measures psychological impact [61].

● Functional couple relationship - systemic core outcome measure (SCORE 15) measures relationship changes [62].

● Use of health services and erectile dysfunction medication/technologies, collated via a self-report questionnaire designed by the investigators.

Outcome measures will be assessed at baseline, at end of intervention and six months later.

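### The definitive trial's recruitment rate is tied to the time for 68 couples to complete the study, which adds treatment and follow-up time to recruitment time and counts completers, not recruits

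*Protocol article*

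**What the plan says.** The rule is in the protocol article under Patient recruitment, within the phase meant to set the parameters of a definitive trial: "The recruitment rate for a larger definitive trial will be calculated from the time taken for 68 couples to complete the study". The same paragraph says that the site will keep logs of recruitment at baseline and of attrition after randomisation, and that session attendance will be logged.

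Three other sections show what completing involves and which count 68 is:

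- Setting and participants: "Recruitment will take place over one year".
- Phase 1, on the intervention: "It will consist of six sessions [34,35] conducted every two to three weeks". Outcome measures: "Outcome measures will be assessed at baseline, at end of intervention and six months later". A couple therefore completes six months after the sessions end.
- Sample size calculation: "we anticipate contacting approximately 420 patients to recruit 88 couples", which is meant "to achieve a sample size of 68 couples completing the study". Here 88 is the number recruited and 68 the number left after loss to follow-up.

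**The concern.** A recruitment rate needs couples entering the trial as its numerator and time open to recruitment as its denominator. The stated rule departs from both. Its clock runs until a couple finishes, so it includes a fixed lag of sessions and follow-up that has nothing to do with how fast couples join. Its count, on the usage in the sample size section, is what remains after attrition.

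This matters because the study is a pilot. Its third objective includes determining recruitment for a definitive trial, and this sentence is the only rule the article gives for that trial's recruitment rate. A planner who used the resulting figure as a rate of entry would ask for too many sites or too long a recruitment period, or might judge a workable trial infeasible. The rule is also weakest when recruitment is slow: if fewer than 68 couples complete, the time it depends on does not exist.

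**Working it through.** **Inputs from the protocol article.** Recruitment period 12 months; 88 couples recruited; 68 completing; about 420 patients contacted at 21% uptake; six sessions two to three weeks apart; last assessment six months after the end of the intervention.

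**Assumptions.** Even accrual; first session at recruitment; control couples assessed on the same timetable; the 68th completer is among the last couples recruited. Any wait before the first session would lengthen the lag.

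**Step 1: reproduce the plan's figure.** 68 × 1.30 = 88.4 and 420 × 0.21 = 88.2, so both routes give the stated 88. The implied loss is (88 − 68)/88 = 22.7%, and the implied retention 68/88 = 77%.

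**Step 2: lag from recruitment to completion.** Six sessions have five gaps: 5 × 2 = 10 weeks to 5 × 3 = 15 weeks, or 2.3 to 3.45 months. Adding six months gives 8.3 to 9.45 months.

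**Step 3: time to the 68th completion.** T = 12 + lag = 20.3 to 21.45 months.

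**Step 4: compare the rates.**

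- Couples recruited per month open: 88/12 = 7.33.
- The rule read as 68/T: 68/20.3 = 3.35 to 68/21.45 = 3.17.
- Ratio: 3.35/7.33 = 0.46 to 3.17/7.33 = 0.43, so 54 to 57% too low.

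**Step 5: separate the two sources.** With the same couples in both rates (88/T against 88/12, or 68/T against 68/12), the ratio is 12/T = 0.59 to 0.56, so 41 to 44% too low. That part comes from the added time alone. Counting 68 instead of 88 takes the shortfall past half.

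**Step 6: vary the assumptions.** Unless stated, 68/T is set against the rate of couples recruited.

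| Scenario | Shortfall |
|---|---|
| Planned figures | 54–57% |
| 90% retention | 50–53% |
| 100% retention (68th recruit at 68/7.33 = 9.27 months) | 47–51% |
| 88 couples take 18 months to recruit | 47–49% |
| 88 couples take 24 months to recruit | 43–45% |
| Completion means end of sessions only (T = 14.3–15.45) | 35–40% |
| Like-for-like count on planned figures | 41–44% |

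The direction is the same in every row.

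**Step 7: can the 68th completion fail to occur?** The plan has almost no slack. At 20% uptake instead of 21%, 420 × 0.20 = 84 couples enter, and at 77% retention 84 × 68/88 = 64.9, about 65, complete. With recruitment limited to one year, the rule then has no value as written.

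**The case against.** The strongest defence has four parts.

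- **The formula is inferred.** The sentence says only that the rate is calculated from a time. It gives no numerator or denominator, and nothing prevents an allowance for the fixed treatment and follow-up periods. The article also uses 68 loosely: the abstract gives it as the number to be randomised, and the sample size section opens with it as the number to recruit, "with 30% over-recruitment to enable adjustment for loss to follow-up". This part stands as a limit on the size of the error. It does not rescue the rule, because completion time is still the wrong starting point and no allowance is stated.
- **The right data will exist.** The logs cover baseline recruitment and later attrition, and the Phase 3 section refers to calculating recruitment and retention rates. A reader might infer that the rule hides whether uptake or retention is the bottleneck. The documents do not support that, since the two are recorded separately. What remains is that the rate named for the definitive trial is not the one built from those logs.
- **The planning harm needs a further mistake.** A reader might infer that the rule would more than double the sites or the time needed. That follows only if a completers-per-month figure is applied to a target of couples randomised (7.33/3.35 = 2.2 to 7.33/3.17 = 2.3 times) and the logged rates are ignored. Against a target of completers, the inflation is 20.3/12 to 21.45/12, about 1.7 to 1.8 times.
- **A shortfall could be handled.** The same calculation could use whatever number completes. That is reasonable, but the sentence fixes 68.

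**Conclusion.** The point holds as a defect in the stated definition. The rule bases a recruitment rate on completion time and, by the article's own usage, on completers. Read as 68/T with even accrual and the planned attrition, it is about 54 to 57% too low; on a like-for-like count it is about 41 to 44% too low.

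A reader might take from the first range that the rule understates recruitment by more than half in general. The documents do not support that: the figure depends on the inferred formula and on the planned attrition and accrual, and the shortfall is about half or less under several plausible alternatives.

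The correction is worth making because the sentence concerns a named objective of the pilot. It is not critical. It touches no participant, allocation, outcome or primary analysis, and the correct rate can still be recovered from the logs after the trial ends.

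**What to change.** Replace the one sentence. Define the recruitment rate for the definitive trial as couples randomised divided by the number of months the clinic was open to recruitment, with a 95% confidence interval, taken from the recruitment logs already planned. On the planned figures, and treating the count as Poisson, this would be 88/12 = 7.3 per month, with an approximate interval of (88 ± 1.96 × √88)/12 = 5.8 to 8.9.

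Carry two logged quantities separately into the planning of the definitive trial, in place of one completion-based rate: the proportion of contacted patients whose couple is randomised (planned 21%), and the proportion retained at the end of the intervention and at six months (planned 68/88 = 77% completing). The number completing can then be projected as rate × months × retention, and it is defined whether or not 68 couples finish.

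The cost is a wording change, with no new data collection and no change to the design.

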##### Route 1: outpatient surgical urology follow-up clinic

Participants will be recruited from the outpatient surgical urology follow-up clinic. Clinic nurses will approach potentially eligible patients and invite them to complete the EPIC screening measure. Participants who are eligible based on the EPIC score will be verbally notified, given detailed information about the study, and provided with baseline questionnaires and consent forms. A member of the research team will be on hand to answer any questions that patients may have.

When a nurse is not available, the study will be introduced by the consultant/registrar during the consultation; if interested in the study, the patient will then be introduced to the researcher, who will provide detailed information about the study and invite them to complete EPIC.

##### Route 2: postal invitation from clinical team

This route will be adopted on days when the clinic is very busy and there is consequently limited private opportunity for completing the EPIC screening tool. A letter and detailed information sheet is sent to patients who are potentially eligible. The letter invites them to complete and return the EPIC questionnaire. The research team will write to tell patients whether or not they are eligible; if eligible, the remaining baseline questionnaires and consent forms are also issued at this time.

#### Randomisation, allocation concealment and blinding

Once consent is gained and baseline data (outcome measures and demographics) are returned, patients will be randomly assigned using block randomisation with a 1:1 allocation ratio to receive the intervention or standard care comprising their usual follow-up hospital appointments. The allocation sequence is generated using computer software (GraphPad Software, La Jolla, CA, USA) that randomly assigns subjects to the control and intervention arms in blocks of 20. This block randomisation process ensures equal numbers in the intervention and control arms and removes selection bias [58].

A research administrator, who has no involvement in the study, will assign participants to the control or intervention arm according to the allocation sequence described above. This individual will not be aware of the allocation sequence until the moment of assignment.

In line with other designs of this type [59], blinding will not be possible due to the nature of the intervention and the acceptability component of the study. It will be clear to study participants that they have been allocated to the intervention or control group due to the timing of data collection relative to receipt of the intervention.

In order to establish if the intervention and control group are clinically similar, the two groups will be compared by physical health status. Consequently, the hospital’s audit officer will provide the research team with anonymous data relating to clinical markers of disease pathology. The markers are: (1) prostate-specific antigen (PSA), a protein produced by the prostate that can be measured in a man’s blood serum and used as a prognostic indicator; when combined with (2) the Gleason score (GS), to differentiate the grade of tumour (from low- to high-grade malignancy); along with (3) the tumour, node and metastases (TNM) staging system to distinguish localised from locally advanced and metastatic disease (the degree of spread and involvement of lymph nodes) [60]. This clinical data will allow the team to determine whether physical health status may be a confounding variable in explaining any variance in the results of the trial.

In addition, ineligibility data will be recorded noting number of patients and the reasons for their ineligibility. Reasons for non-participation or withdrawal from the study will be recorded to understand the acceptability or otherwise of the support. However, in keeping with ethical practice, potential participants will not be asked for reasons for non-participation; this will only be noted if proactively provided by patients or partners.

The recruitment and randomisation process is set out in the CONSORT schema in Figure 1.

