## Background

Surgery is a major treatment modality for prostate cancer [1] and has been hypothesised to reduce mortality more than other treatments for localised prostate cancer [2]. However, the risks of surgery are known to include erectile dysfunction [3] even when nerve-sparing approaches are used [4]. Long-lasting sexual and urinary difficulties are the most common and troubling side-effects following radical prostatectomy [5] alongside loss of libido, ejaculatory dysfunction, orgasmic dysfunction and penile shortening [6]. Even at 24 months post-operatively, most men have not returned to their baseline measure of sexual function prior to surgery [7]. These side-effects can be distressing for men and their partners due to the impact on psychological well-being and couple intimacy [8-11].

Many men affected by prostate cancer and erectile dysfunction experience symptoms of anxiety and depression [12,13], with reduced quality of life directly associated with urinary and sexual body-image changes that occur after surgery [14]. Partners of these men also experience considerable psychological distress [9,15-17], with anxiety and depression often reported at higher levels for partners than for patients [18,19]. The difficulties experienced after surgery can also impact on the couple relationship itself; for instance, erectile dysfunction is associated with reduced wellbeing [20,21] and lower levels of dyadic adjustment in the first year after surgery [22].

Prostate cancer has been described as a ‘relationship disease’ [23] and it has been established that couples affected by prostate cancer often have significant unmet psychosexual supportive care needs around sexual recovery and rehabilitation [24,25]. With such evidence of the impact of sexual dysfunction on relationships, there has been increasing interest in the development of couple-based psychosocial interventions that aim to improve wellbeing and relationship quality. Couple-based interventions have been effective in reducing psychological distress [26] and facilitating healthy communication [27,28]. Sexual rehabilitation therapy has been particularly helpful in increasing use of erectile dysfunction medications [29] and re-establishing a sexual relationship [30,31].

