#### Eligibility

Eligible patients are all men who: (1) are >11 weeks post-operative for localised prostate cancer (to recruit men who have recovered from the immediate effects of surgery and who have consequently started to regain some functioning); (2) have received surgery in the previous two years (since long-term adaptation will have commenced in patients who have had surgery beyond this timeframe); (3) have a partner (in an established same-sex or different-sex relationship); (4) score ≤60 (the clinical threshold for potency [42]) on the sexual function domain of the Expanded Prostate Cancer Index Composite (EPIC).

Patients are excluded from the study if: (1) they have a prognosis of ≤1 year (most men who have had recent surgery will have a good prognosis, so it is unlikely that many men will be excluded by this criteria); (2) they reside in Dumfries and Galloway (to prevent excess burden travelling to the intervention site); (3) they cannot provide informed consent; (4) they are unable to communicate in English (this is a pilot trial, and if we move to a full-scale trial in future we would seek to include interpreters/translators).

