#### Data storage and confidentiality

Participants will be assigned a study number. All documents will be labelled with the study number alone, and data stored on computers will only use this number. All names referred to in the interviews will be changed following transcription and saved under the assigned study number. Pre-anonymised transcripts will then be deleted.

Identifiable personal data will only be retained in the following circumstances: consent forms will be stored in a locked filing cabinet; couple names/addresses will be stored in a locked filing cabinet and a password-protected computer used in disseminating outcome measures and final report/s.

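### Comparing the arms on anonymous disease markers cannot show whether health status explains the outcome, and the stated ANOVA leaves baseline EPIC and time since surgery unused

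*Protocol article*

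**What the plan says.** Under Randomisation, allocation concealment and blinding, the protocol article sets out a check on the comparability of the arms: "In order to establish if the intervention and control group are clinically similar, the two groups will be compared by physical health status". The data come from outside the trial team. The hospital's "audit officer will provide the research team with anonymous data relating to clinical markers of disease pathology", namely PSA, Gleason score and TNM stage. The purpose is to let the team "determine whether physical health status may be a confounding variable in explaining any variance in the results of the trial". The section does not say whether the records carry the study number. It describes 1:1 allocation in blocks of 20 and names no stratification factor.

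On identifiers, Data storage and confidentiality says: "All documents will be labelled with the study number alone, and data stored on computers will only use this number".

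Under Eligibility, entry is for men who "are >11 weeks post-operative for localised prostate cancer" and who "have received surgery in the previous two years". The lower limit is explained by recovery of some function, and the upper limit by the start of long-term adaptation.

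Statistical analysis describes an ANOVA of the group-by-time interaction with two measurement points, end of intervention and six-month follow-up. It names no covariate. The same section bases the efficacy estimate on mean differences between arms before and after treatment. Sample size calculation says that the standardised difference observed will size the definitive trial.

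**The concern.** The method described does not lead to the conclusion claimed for it. For a baseline variable to distort the comparison, it must differ between arms and must also predict the outcome. The arm comparison addresses only the first condition, and after proper randomisation any difference it finds is a chance one. It says nothing about the second, which is the part that concerns explaining variance in the results. That needs each man's marker values set beside his own EPIC score.

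Meanwhile two variables with a more direct bearing on EPIC do not appear in the stated model. One is baseline EPIC itself. The other is time since surgery, which spans a window that the article defines by stage of recovery. At stake is the precision of the efficacy estimate, which matters because that estimate is to be carried into the next trial's sample size.

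**Working it through.** **1. What the check can and cannot show.** There are two readings of *anonymous*.
- Literal: no key joins a marker record to an EPIC score. Only arm summaries can be compared, and the stated aim cannot be met.
- Coded: records carry the study number and could be linked. The aim could then be met, but the only use described is still the arm comparison, which does not meet it.

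On either reading the claim does not follow from the procedure as written.

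**2. The plan's own figures.** For the repeated-measures interaction, λ = f²·N·m/(1 − ρ) with df 1 and N − 2. With f = 0.20, N = 68, m = 2 and ρ = 0.5 (assumed, because the article does not state it), λ = 0.04 × 68 × 2 / 0.5 = 10.88 and power is 0.90. The stated 68 is reproduced. The 9.6-unit target is 2 × 0.20 × 24 = 9.6, from the stated f and SD.

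**3. Chance imbalance in time since surgery.** With 34 per arm, the standard error of a standardised baseline difference is √(2/34) = 0.243. An imbalance above 0.25 SD in either direction has a probability of about 30%, and above 0.5 SD about 4%.

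The resulting shift in the unadjusted arm mean difference has SD r × 24 × √(2/34), where r is the correlation of time since surgery with follow-up EPIC. The documents give no value for r; 0.2 to 0.4 is an assumption.

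| r | SD of shift | 95% range (×1.96) | Variance removed by adjustment (r²) |
|---|---|---|---|
| 0.2 | 1.16 | ±2.3 | 4% |
| 0.3 | 1.75 | ±3.4 | 9% |
| 0.4 | 2.33 | ±4.6 | 16% |

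These are upper values for each r. If r is taken after adjustment for baseline EPIC, the residual SD should replace 24. With a baseline–follow-up correlation of 0.5 (assumed), the residual SD is 24 × √(1 − 0.25) = 20.8, and the ranges for r = 0.2 and 0.4 fall to about ±2.0 and ±4.0.

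**4. The shift and the variance reduction are one loss.** The unadjusted standard error of the arm difference is 24 × √(2/34) = 5.82. At r = 0.4, removing the shift leaves √(5.82² − 2.33²) = 5.33, which equals 5.82 × √(1 − 0.16). The two columns must not be added together as separate harms.

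**5. Baseline EPIC.** For a baseline–follow-up correlation of 0.3, 0.5 or 0.7 (assumed), adjustment cuts the variance by 9%, 25% or 49%. The standard error falls from 5.82 to 5.55, 5.04 or 4.16. Entry is restricted to scores of 60 or below, which may hold this correlation down.

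**6. Consequence for the next trial.** Required n varies with 1/difference². If the true difference is 9.6 and SD is held at 24, a shift of ±3.4 (the 95% extremes at r = 0.3) multiplies the resulting n by (9.6/13.0)² ≈ 0.5 or (9.6/6.2)² ≈ 2.4. Total sampling error is larger, at ±1.96 × 5.82 = ±11.4. Time since surgery accounts for a minor part of it, but an avoidable part.

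**The case against.** **Linkage.** A reader might infer that the markers cannot be linked to outcomes. The article does not say that. Its confidentiality section describes transcripts this way: "All names referred to in the interviews will be changed following transcription and saved under the assigned study number". It then calls the preceding files pre-anonymised, so anonymised data in its usage can be coded and linkable. An arm comparison in any case needs records tied at least to allocation. This objection stands: linkage is unstated, not excluded.

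**Drivers of recovery.** A reader might also infer that the article identifies time since surgery and nerve-sparing as what drives recovery. It does not. Nerve-sparing appears only in the Background, to say that erectile dysfunction occurs despite it. The statement "Even at 24 months post-operatively, most men have not returned to their baseline measure of sexual function prior to surgery" compares men with their own pre-surgery level and gives no gradient inside the entry window. What the text supports is narrower: the eligibility limits are justified by stage of recovery, so time since surgery is a plausible covariate, with a strength that has to be assumed.

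**Choice of markers.** It is tempting to add that TNM hardly varies once entry is limited to localised disease. Some pathological variation may remain, PSA and Gleason score can still differ between men, and describing arms on clinical markers is ordinary reporting.

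**Omission.** Covariate lists are often left to an analysis plan, unstratified blocks are legitimate in a single-site pilot, and the demographic form is not shown. So *unused* can mean only unused in the model as stated. The confounding claim, however, is written text and does not depend on what another document may add.

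**Size.** The shift concerns the arm mean difference. In the interaction between the two post-baseline points, a prognostic effect that is constant over time cancels. Chance imbalance is also already reflected in the standard error of an unadjusted test, so validity is not affected.

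**Pilot status.** Feasibility and acceptability are the primary aim, and the article says it does not formally test hypotheses. This limits the weight of the point. It does not remove it, because the observed difference is to size a definitive trial.

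**Conclusion.** The point holds in this form: the arm comparison on PSA, Gleason score and TNM cannot determine whether physical health status explains variance in the results, and the article does not state the linkage that would be needed. The stated ANOVA also leaves out two baseline variables that are to hand.

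The consequence is lost precision and exposure to chance imbalance. A reader might conclude that the trial's results will be confounded; randomisation rules out that systematic reading.

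The size rests on an assumed correlation of 0.2 to 0.4 between time since surgery and EPIC, SD 24 and 34 per arm. On those terms the chance shift in the arm mean difference is at most about ±2.3 to ±4.6 units (95% range) against 9.6, and smaller with a baseline-adjusted residual SD. Feasibility conclusions are untouched. The correction is an inexpensive improvement to the efficacy estimate.

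**What to change.** 1. Estimate the arm difference in EPIC sexual function with baseline EPIC and time since surgery as pre-specified covariates, by ANCOVA at each follow-up or by a mixed model over both. Fix the functional form of time since surgery in advance.
2. Have the audit officer supply PSA, Gleason score and TNM under the study number, after confirming that consent covers the linkage. State this in place of the bare word *anonymous*.
3. Report the three markers by arm descriptively.
4. Delete the statement that the arm comparison will determine confounding.

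The cost is one or two degrees of freedom, a consent check and a few sentences of wording. Baseline EPIC is already collected, and the date of surgery is needed to apply the eligibility window, so no new patient burden arises.
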